### Data Collection Tools and Procedures

#### Overview

Data will be collected at 3 time points: baseline, week 8 (following completion of the intervention), and week 16 (following the 8-week postintervention observation period). Objective app use data will be collected via the Calm app, which will record the day and time of every app session; the duration of sessions; the type of session (eg, meditation, sleep story, and breathing exercise); and title of sessions (eg, Daily Calm and Daily Move) performed during the study period. Table 2 shows the primary and secondary outcome measures collected at each administration time point.

**Table 2 table2:** Primary and secondary outcome measures at each administration time point.

Measure			Assessment		Baseline		8-week follow-up		16-week follow-up		Continuous data collection
**Primary outcomes**											
	Meditation adherence	Objective app use data		N/A^a^		N/A		N/A		Yes	
	Anchoring plan adherence	Objective app use data		N/A		N/A		N/A		Yes	
**Secondary outcomes**											
	Stress	Perceived Stress Scale		Yes		Yes		Yes		N/A	
	Anxiety	Hospital Anxiety and Depression Scale		Yes		Yes		Yes		N/A	
	PTSD^b^	Impact of Events Scale—Revised		Yes		Yes		Yes		N/A	
	Sleep disturbances	Insomnia Severity Index		Yes		Yes		Yes		N/A	
	Habit strength	Self-report Behavioral Automaticity Index		Yes		Yes		Yes		N/A	

^a^N/A: not applicable.

^b^PTSD: posttraumatic stress disorder.

#### Primary Outcomes: Adherence Maintenance (Objective App Use Data)

The primary outcomes for this study measure participants’ ability to maintain adherence to the ≥10 minute-per-day meditation prescription over the 16-week study period. Specifically, we will measure meditation adherence as a binary variable equal to 1 if participants complete ≥10 minutes of meditation for ≥4 days per week and 0 otherwise. This meditation adherence outcome will be defined weekly during both the 8-week intervention and the 8-week postintervention observation periods. We will also measure objective meditation app use using the number of days with ≥10 minutes of meditation per week and the total number of meditation minutes per week, both of which will allow us to investigate the behavioral frequency of app-based meditation and improve the statistical power of our analyses. We will also augment these objective app-based meditation measures with a self-reported measure of days with any meditation (ie, either using the app or meditation outside the app) over the past week that is assessed at baseline, week 8, and week 16 time points. We will measure anchoring plan adherence as a binary variable equal to 1 if participants complete ≥10 minutes of meditation within 1 hour of the timing of their chosen anchor for ≥4 days per week and 0 otherwise. Similar to overall meditation, we will also measure anchoring plan adherence as the number of days completing ≥10 minutes of meditation within 1 hour of the timing of their chosen anchor per week.

#### Secondary Outcomes: Stress, Anxiety, and Posttraumatic Stress Disorder

We will assess stress at baseline, week 8, and week 16 using the PSS-10. The PSS is a 10-item self-report inventory that assesses the degree to which individuals have felt stressed during the past month [106]. The PSS is a widely used measure of self-reported stress that has demonstrated acceptable validity and reliability in previous research [107]. We will also assess anxiety symptoms at baseline, week 8, and week 16 using the Hospital Anxiety and Depression Scale. The Hospital Anxiety and Depression Scale is a 14-item self-report inventory that assesses the severity of anxiety and depressive symptoms during the past week [108]. For our purposes, we will only be focusing on the anxiety subscale. Finally, we will assess posttraumatic stress disorder (PTSD) symptoms at baseline, week 8, and week 16 using the Impact of Events Scale—Revised. The Impact of Events Scale—Revised is a 22-item self-report inventory that assesses the severity of PTSD symptoms (eg, trouble sleeping, irritability, and jumpiness) over the past 7 days [109]. The instructions were modified to include PTSD symptoms resulting from specific trauma or from the ongoing COVID-19 pandemic.

#### Secondary Outcome: Sleep Disturbances

We will assess sleep disturbances at baseline, week 8, and week 16 using the Insomnia Severity Index (ISI). The ISI is a 7-item self-report inventory that assesses the severity of sleep problems, noticeability of sleep problems, stress resulting from sleep problems, and the perceived impact of these problems on daily functioning and quality of life [110]. The ISI is a valid and reliable measure that has demonstrated excellent internal consistency in previous research [111].

#### Secondary Outcome: Habit Strength

We will assess habit strength at baseline, week 8, and week 16 using the Self-Report Habit Index (SRHI). The SRHI is a brief self-report inventory that assesses the perceived habit strength (ie, automaticity) of a specific behavior, such as meditation [112]. The SRHI has been used to assess habit strength in a wide range of behaviors and has demonstrated adequate reliability in previous research [112].

#### Demographic Information

The following demographic information will also be collected from participants at baseline assessment: age; gender; race; Hispanic status; employment information (ie, status, hours, and work from home); annual household income; number of adults and children in the household (if any); marital status; education level; past mental health diagnosis (ie, PTSD and depression); current mental health medications (if any); self-rated physical health (5-point Likert scale); and any current chronic medical condition diagnosis (eg, high blood pressure, diabetes, and asthma).

#### Satisfaction

Participant satisfaction will be assessed at weeks 8 and 16. All participants will be asked to rate their overall enjoyment and satisfaction with the Calm app and the study itself, as well as their intent to continue using the app along with the app features (eg, mood tracking and session tracking) and app content (eg, daily meditations, sleep meditations, and soundscapes) that they found most helpful for maintaining their daily meditation practice. Then, participants will be asked specific questions regarding their chosen meditation anchor, such as how easy it was to select and use their chosen anchor during the intervention, their intent to continue using their meditation anchor, and the helpfulness of the anchoring plan in maintaining their meditation practice. Participants in the intervention groups will also be asked questions related to the incentives, including how easy it was to understand the incentive process; how easy it was to earn incentives; if they liked the incentive options, how motivated they were by the incentives; and if there was anything that would have motivated them more. This information will provide helpful qualitative data that can be used to improve future adherence studies, including the types of anchoring strategies that are most successful in establishing a meditation habit and what motivates people to establish and maintain an app-based meditation habit.

Attrition will be assessed at all stages of the study: (1) enrolled but did not complete the baseline assessment, (2) completed baseline assessment but lost to follow-up during the 8-week intervention period (ie, did not complete week 8 assessment), and (3) completed the 8-week assessment but lost to follow-up during the 8-week postintervention observation period (ie, did not complete the week 16 assessment).

### Intervention

#### Randomization and Baseline

This randomized controlled trial aims to test the effectiveness of different strategies on adherence to the daily ≥10-minute meditation prescription via a mindfulness meditation app. Note that the meditation prescription and the anchoring plan are not interventions; rather, the interventions are the additional supports that are provided for the anchoring plan to establish an app-based meditation habit. After randomization, all participants will complete a web-based baseline survey to collect additional demographic information and to assess the baseline levels of the secondary outcome measures listed in the previous sections.

#### Introductory Video

Immediately following the web-based surveys, participants will then watch 1 of 3 brief 5-minute introductory videos that will vary slightly based on their experimental conditions. All 3 videos will contain background information on the benefits of mindfulness meditation and habit formation (eg, previous research and theory); a sample anchoring plan (eg, “After [insert behavior here], I will meditate for 10 minutes”); a study timeline (ie, baseline assessment, 8-week intervention period, follow-up assessment, 8-week postintervention period, and second follow-up assessment); and compensation information for completing the 3 web-based surveys (US $20 gift card). In addition to these foundation elements, participants in the NTCI and TCI groups will be told in the video that they are eligible for incentives every 2 weeks during the 8-week intervention period conditional on either meditating at any time (NTCIs) or meditating using their anchoring plan (TCIs). The video for the usual Calm condition will only include the foundation elements mentioned previously, with no mention of incentives or personalized feedback messages. Information in all 3 videos will be presented by a member of the study team using both written and spoken texts. Participants in the NTCI and TCI groups will also receive instructions regarding prize eligibility as detailed in the *Study Design* section.

#### Anchoring Plan Worksheet

After watching the introductory video, participants will complete a video comprehension quiz to ensure that they understand the study timeline and requirements. Participants must score 100% on the quiz to move on with the study. Then, all participants will be asked to complete a web-based worksheet to help them develop a meditation anchoring plan. This worksheet will first ask participants to fill out a basic implementation intention plan (ie, “After _____, I will meditate for 10 minutes”) based around a routine behavior (ie, their anchor) they perform in the morning, given that previous research suggests the morning habits are easiest to form [31]. Next, participants will be instructed to add additional details to their anchoring plan to make it more specific (eg, anchor timing and anchor location), as generic plans may not be as effective as plans that specifically outline when and where this behavior will occur. After finalizing their anchoring plan, the participants will be emailed a copy of their anchoring plan for their records.

#### Intervention, Postintervention, and Follow-up Surveys

The 8-week intervention period will begin once the participants complete the baseline assessment and anchoring plan worksheet. All the participants will be asked to meditate for ≥10 minutes every day during the intervention period. Every 2 weeks, participant use data will be checked to determine incentive eligibility for participants in the NTCI and TCI groups. Every week, all the participants will also receive a text message from the study team as a reminder to continue meditating using their chosen anchor. In addition, participants in the BM group will receive a message focused on self-monitoring of their meditation behavior every 2 weeks that informs participants of the number of ≥10-minute meditations they completed during the past 2 weeks. Participants in the self-monitoring of outcomes of behavior messages groups will receive a message focused on self-monitoring of outcomes of their meditation behavior (ie, mood tracking) every 2 weeks that encourages the participants to keep track of their mood using the “How Are You Feeling?” feature in the Calm app. After 8 weeks, participants will be emailed a link to complete the first of the 2 follow-up surveys. These surveys will assess any improvements in the secondary outcome measures assessed at baseline, as well as their satisfaction with both the Calm app itself and the interventions. Following the completion of the 8-week intervention period and the week-8 follow-up survey, participants will be asked to continue using their anchors to strengthen their meditation habits during the 8-week postintervention observation period. However, unlike in the intervention period, participants in all intervention groups will no longer receive weekly reminders, biweekly self-monitoring messages, or incentives during the postintervention period. Participants will then be contacted at week 16 to complete the second follow-up survey to assess changes in the secondary outcome measures at week 16.

### Data Analysis Plan

To examine our specific aims, statistical analyses comparing group-level differences in the primary and secondary outcome measures will be performed. First, an analysis of covariance framework will be used to test for group-level differences in each primary and secondary outcome, controlling for participant characteristics that are found to significantly differ between study groups at baseline. For analyses of dichotomous outcomes, such as meditation regularity at weeks 8 and 16, a nonparametric McNemar test and multiple logistic regression that controls for additional participant-level covariates will be used to assess study group differences. In addition to static comparisons of group means for each outcome, the longitudinal nature of the app use data will be leveraged by using repeated measures and time-series techniques. Specifically, a linear mixed model with repeated observations will be fitted using maximum likelihood through “xtmixed” in the software package Stata (StataCorp) to study group-level temporal dynamics in the primary and secondary outcomes.

To estimate the impact of our intervention on our static primary outcomes of meditation regularity and anchoring plan regularity at weeks 8 and 16, we will use logistic regressions with the following specifications.

Our main unadjusted model will have the following form:

Pr(y_i_) = exp(*β*_0_+ *β*_1_T + *β*_2_T2 + *β*_3_T3 + *β*_4_T4 + ε_i_  **(1)**

Our main adjusted model has the following form:

Pr(y_i_) = exp(*β*_0_+ *β*_1_T + *β*_2_T2 + *β*_3_T3 + *β*_4_T4 + X_i_
*β*_5_ + ε_i_  **(2)**

where *y_i_* is a binary variable equal to 1 if individual i completed ≥10 minutes of meditation for ≥4 days during week 8 of the study; T1 is an indicator for treatment group 1 (that receives self-monitoring behavior messages and NTCIs); T2 is an indicator for treatment group 2 (that receives self-monitoring outcome messages and NTCIs); T3 is an indicator for treatment group 3 (that receives self-monitoring behavior messages and TCIs); T4 is an indicator for treatment group 4 (that receives self-monitoring outcome messages and TCIs); and *ϵ_i_* is the idiosyncratic error. The coefficients of interest are *β*_1_ through *β*_2_. Equation 2 has the term *X_i_β*_5_, which includes a vector of the following observable participant characteristics (*X_i_*): age, education, sex, race, ethnicity, household income, self-reported mental and physical health, baseline meditation habit strength, intrinsic motivation for meditation, and measures of time and risk preferences and the respective coefficients (*β*_5_). For more information on our data analysis plan, please see Multimedia Appendix 1.

In addition, we will investigate potential intervention moderators and mediators. Specifically, we will use the same regression models specified earlier in this section and include additional interaction terms between each study group indicator variable and a single moderating variable measured at baseline. Significant coefficients estimated for these interaction terms will be used to identify the moderating effects of participants’ baseline characteristics, such as age, gender, race, and employment information. In addition, we will separately examine the mediating effects of anchoring plan adherence and habit strength at the end of the intervention on the maintenance of mediation following the procedures outlined by Judd and Kenny [113]. We will first regress meditation measured in week 16 on indicator variables for each study group and then regress meditation in week 16 on indicator variables for each study group as well as anchoring plan adherence measured over the first 8 weeks (ie, during the intervention). The mediating effect of anchoring plan adherence (our third hypothesis) will be calculated by subtracting the coefficients estimated in the first regression from those in the second regression. We will also use these procedures to investigate the mediating effect of habit strength measured at week 8 (ie, immediately after the intervention). We will also use a modern mediation analysis technique that allows for additional covariates when estimating the direct and indirect treatment effects in the equations described earlier [114].

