### Study Design

This study will use a 5-arm, parallel, partially blinded (participants only) randomized controlled design. After completing a web-based eligibility survey, the participants will be randomized into 1 of the 5 study groups. Stratified randomization methods will be used to ensure that race and ethnicity (ie, Hispanic) are equally represented across study groups. The 5 study groups include a control group that will use the anchoring plan to form a meditation habit with Calm and then receive no additional intervention supports, while the 4 intervention groups will also use the anchoring plan in combination with 1 of the 2 different types of self-monitoring messages and 1 of the 2 different forms of incentives. Participants in the 4 intervention groups will also be eligible for an in-kind reward (eg, Calm t-shirt, Calm tote bag, or Calm water bottle; all gifts have a retail value of roughly US $25 but a wholesale cost of US $5) conditional on either completing ≥10 minutes of meditation at any time of day on at least 8 days over a 2-week period (NTCIs) or completing ≥10 minutes of meditation within a 2-hour window around the time their chosen anchor typically occurs during the day (ie, anchor time1 hour) on at least 8 days over a 2-week period (TCIs). All additional interventions to support adherence to the anchoring plan will be delivered for 8 weeks; thus, participants are eligible to win up to 4 in-kind incentives during the intervention period. Participants within the intervention groups will also be randomly assigned to receive either messages that focus on self-monitoring of behavior (eg, “You completed a meditation session using your Calm app on at least 8 days during the past 2 weeks”) or messages that focus on self-monitoring of outcomes of behavior (eg, “We encourage you to continue using the ‘How Are You Feeling?’ check-in feature after completing your meditation sessions”). The “How Are You Feeling?” check-in feature is an existing feature available to all users of the Calm app that allows users to record their current mood state (eg, happy, sad, or anxious). The fractional factorial study design is shown in Table 1.

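### ANCOVA covariates are picked by baseline significance tests, which makes the model depend on chance and gives up precision on the secondary scales

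*Protocol article*

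**What the plan says.** The Data Analysis Plan opens with a general rule. Its scope is wide: "an analysis of covariance framework will be used to test for group-level differences in each primary and secondary outcome". The rest of that sentence sets how the covariates are chosen: "controlling for participant characteristics that are found to significantly differ between study groups at baseline". It gives no significance level for the screen and names neither the baseline score of the outcome nor the randomisation strata as ANCOVA covariates.

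For dichotomous outcomes the same paragraph turns to a McNemar test and a "multiple logistic regression that controls for additional participant-level covariates will be used to assess study group differences". The section then specifies Equations 1 and 2: for the "static primary outcomes of meditation regularity and anchoring plan regularity at weeks 8 and 16, we will use logistic regressions". Equation 1 is labelled unadjusted. Equation 2 "includes a vector of the following observable participant characteristics", and that list is fixed in advance; it begins "age, education, sex, race, ethnicity, household income, self-reported mental and physical health, baseline meditation habit strength, intrinsic motivation for meditation". A linear mixed model with repeated observations is also planned for the primary and secondary outcomes.

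Two other sections bear on this. Under Study Design, "Stratified randomization methods will be used to ensure that race and ethnicity (ie, Hispanic) are equally represented across study groups". Table 2 and the secondary-outcome sections show that all five secondary scales are measured at baseline, week 8 and week 16.

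**The concern.** Randomisation makes the arms comparable in expectation. The baseline questionnaires are completed after randomisation but before the arm-specific introductory video, so the intervention cannot yet have affected them. A significant baseline difference is then a chance event, and testing for it says nothing about whether the covariate predicts the outcome. A screen on imbalance has two consequences:

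- **The model is unknown until the data are seen.** Which covariates enter depends on chance, and the set may change with the cut-off, which is not stated.
- **The useful covariates are usually dropped.** For a repeated scale, its own baseline score is usually the covariate of most value, yet it enters only if it happens to be imbalanced. Race and ethnicity, balanced by the stratification, would rarely pass the screen.

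At stake is the precision of the comparisons on the secondary scales, and whether their adjusted estimates come from a model fixed in advance.

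**Working it through.** **Inputs from the protocol article.** Five arms, 111 per arm, 20% attrition, 88 per arm analysed, power 0.82, Cohen h = 0.43 (Sample Size). Thirteen characteristics are listed under Demographic Information, two of them the stratification factors.

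**Assumptions.** Two-sided alpha 0.05 and a 0.05 screen, since neither level is stated. The correlation r between baseline and follow-up score is not given, so 0.3 to 0.7 is used. For a continuous secondary scale a standardised difference d = 0.43 is assumed, numerically equal to the plan's h.

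**Step 1. The plan's own figure.** Power = Φ(h·√(n/2) − 1.96) = Φ(0.43 × √44 − 1.96) = Φ(0.89) = 0.814, against the stated 0.82. The figure is reproduced to within one percentage point, so 88 per arm is a sound basis for what follows.

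**Step 2. How often the screen selects something.** One covariate under valid randomisation passes about 5% of the time (4.7% to 5.4% in simulation), so a given baseline score is left out about 95% of the time. If the listed characteristics were independent, the chance that at least one is flagged is 1 − 0.95^13 = 0.49 for all thirteen, and 1 − 0.95^11 = 0.43 without the two stratified ones. Correlated characteristics, or adding the baseline scales to the screen, would change these figures.

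**Step 3. What adjusting for the baseline score is worth.** With a standardised outcome, SE = √(2(1 − r²)/88) and power = Φ(0.43/SE − 1.96). Adjustment multiplies the unadjusted SE by √(1 − r²).

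| r | √(1 − r²) | SE reduction | Power, always adjusted | n per arm for 80% power |
|---|---|---|---|---|
| none (unadjusted) | 1.000 | – | 0.81 | 85 |
| 0.3 | 0.954 | 5% | 0.85 | 78 |
| 0.5 | 0.866 | 13% | 0.91 | 64 |
| 0.7 | 0.714 | 29% | 0.98 | 44 |

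**Step 4. What the stated rule delivers.** Five arms of 88 were simulated, 6,000 runs per setting, with one arm compared with one other. The baseline score was included only when its F test across arms gave p < 0.05.

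| r | Power, unadjusted | Power, screened rule | Power, always adjusted | Type I error, screened rule |
|---|---|---|---|---|
| 0.3 | 0.81 | 0.81 | 0.85 | 0.045 |
| 0.5 | 0.81 | 0.82 | 0.91 | 0.050 |
| 0.7 | 0.81 | 0.83 | 0.98 | 0.044 |

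The screened rule performs almost as if no adjustment had been made. Its type I error stays at or below the nominal level.

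**The case against.** The other side has several fair arguments.

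- **ANCOVA may be meant to imply the baseline score, and Multimedia Appendix 1 may say so.** This is possible: the article does not state that baseline scores are excluded, and the appendix is not at hand. If it does include them, the precision loss in the tables largely disappears. But the sentence says how covariates are chosen and does not name the baseline score. The significance screen is a stated rule, and an unseen appendix cannot be presumed to withdraw it.
- **The mixed model may already use the baseline information.** If baseline is one of the repeated responses, it does. That mitigates the loss for that analysis but not for the ANCOVA.
- **The size rests on an assumed r.** This stands. At r = 0.3 the SE reduction is only 5%, and for stress the PSS-4 entry threshold of 6 narrows the range and may lower r.

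A reader might also infer more than the documents support:

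- **That false positives are inflated.** The simulation shows that they are not.
- **That the primary outcomes lose the same precision.** Meditation and anchoring plan adherence are defined only for the intervention and postintervention weeks, so they have no baseline value to omit.
- **That the strata are ignored throughout.** Equation 2 contains race and ethnicity, and Equation 1 omits covariates because it is the unadjusted model.
- **That the ANCOVA rule flatly contradicts Equation 2.** The reference to each primary outcome makes the two overlap, but the next sentence sends dichotomous outcomes to other methods. This is an ambiguity about which rule governs.
- **That Equation 2 must add the baseline item on "a self-reported measure of days with any meditation (ie, either using the app or meditation outside the app) over the past week".** This is a matter of preference. Eligibility excludes regular meditators, so the item may sit near its floor, and Equation 2 already has baseline habit strength.

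**Conclusion.** The point holds for the ANCOVA covariate rule, and its practical cost falls on the secondary scales. The rule makes the model data-dependent and gives up nearly all the precision that the baseline scores could provide. The size is conditional on r, on the standardised difference of 0.43, on a 0.05 screen, and on the ANCOVA sentence meaning what it says. No figure is put on leaving the strata out of the ANCOVA, because the documents do not show how strongly race or ethnicity predicts these outcomes. For the primary regularity outcomes all that is needed is a statement of which covariate rule applies. The change is worth making because it is cheap, but the primary analysis is not at risk.

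**What to change.** 1. Delete the selection of covariates by baseline significance.
2. Prespecify that each ANCOVA of a secondary scale adjusts for the baseline value of that same scale plus race and ethnicity.
3. In the mixed model, use the baseline score either as a covariate or as one of the repeated responses, not both, and say which.
4. State that for meditation and anchoring plan regularity the fixed Equation 2 list, and not the screened rule, governs the adjusted analysis. Equation 1 can stay as it is.

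The cost is a few sentences in the analysis plan and minor analysis work. The baseline scales, race and Hispanic status are already collected, so data collection and trial conduct do not change.

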### Sample Size

The target recruitment sample size for this study is 555 participants, with 111 participants per study group. On the basis of our existing studies using the Calm app, we anticipate a 20% study attrition, which will yield an effective study group sample size of 88. Our primary measure of meditation app adherence is a binary indicator variable for performing ≥10 minutes of meditation on at least 4 days of the week. This measure of adherence is based on the concept of behavioral regularity, which was proposed by Cheung et al [102] as a standardized measure of treatment adherence. In addition, researchers have recommended that practicing mindfulness for 3 to 4 days per week is the sufficient level of adherence (or regularity) for attaining the mental health benefits associated with meditation, such as stress reductions [103], and this recommendation is theoretically consistent with the notion that a mindful mind is the product of frequent, effortful, and persistent training [104,105]. Thus, we determined our sample size to detect study group differences in meditation regularity at the end of the study (week 16). Using data from our previous studies with Calm, we know that approximately 15% of new Calm users regularly meditate (ie, complete ≥10 minutes of meditation for at least 4 days of the week) 8 weeks after first subscribing to the app and fewer than 10% regularly meditate with Calm 16 weeks after subscribing. An effective study group sample size of 88 provides adequate statistical power (1–β=.82) for detecting study group differences of 18 percentage points in the likelihood of regular mediation in week 16 (Cohen *h*=0.43, which is a small to medium effect size).

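### McNemar's test, a paired-data test, is named for comparing independent arms on meditation regularity; the main logistic models and the sample size do not depend on it

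*Protocol article*

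**What the plan says.** The Study Design section of the protocol article states: "This study will use a 5-arm, parallel, partially blinded (participants only) randomized controlled design". Each person enters one arm only: "the participants will be randomized into 1 of the 5 study groups". Allocation is balanced by strata: "Stratified randomization methods will be used to ensure that race and ethnicity (ie, Hispanic) are equally represented across study groups". That is stratification. Nothing in the article forms matched sets of participants across arms.

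The Data Analysis Plan opens its sentence on binary endpoints with "For analyses of dichotomous outcomes, such as meditation regularity at weeks 8 and 16" and then names two methods for one stated purpose: "a nonparametric McNemar test and multiple logistic regression that controls for additional participant-level covariates will be used to assess study group differences".

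The next paragraph of the same section turns to the static primary outcomes, "meditation regularity and anchoring plan regularity at weeks 8 and 16, we will use logistic regressions with the following specifications". Equation 1 follows, introduced by "Our main unadjusted model will have the following form", and then an adjusted version as equation 2. Both contain indicators for the four treatment arms, with control as the reference.

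**The concern.** McNemar's test compares two proportions measured on the same or matched units, and it uses only the discordant pairs. The stated purpose here is to compare groups of different people. Two uses are conceivable, and neither serves that purpose.

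- **Across arms.** Participants in one arm would have to be paired with participants in another. The article gives no rule for this, so the pairing, and with it the p-value, would be arbitrary. The test also handles two proportions at a time, and the design has five arms.
- **Within participants.** Week 8 and week 16 form true pairs, but the hypothesis tested is then no change over time. The Sample Size section itself expects regular use to fall from about 15% to under 10% among new subscribers. A significant result would be likely with no difference between arms.

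The outcome concerned is a primary one, and week 16 is the time point on which the trial is sized. Left as it stands, the sentence would allow a p-value that does not address the group question to be reported as a planned test of group differences.

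**Working it through.** **1. Does the sample size assume paired or independent groups?**
Inputs from the Sample Size section: "The target recruitment sample size for this study is 555 participants, with 111 participants per study group"; 20% attrition; 88 effective per arm; Cohen h=0.43; an 18-point difference; power 0.82. Alpha is not stated there; I assume two-sided 0.05.

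- Attrition: 111 × 0.80 = 88.8, consistent with 88.
- Arcsine power for two independent proportions: Φ(h√(n/2) − 1.96) = Φ(0.43 × √44 − 1.96) = Φ(2.852 − 1.960) = Φ(0.892) = 0.814, against the stated 0.82.
- h=0.43 corresponds to 15% against 33% (h=0.428). For 10% against 28%, h=0.472.

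The stated power is thus an independent-groups figure. Power for an unpaired z test (pooled variance) at 88 per arm is 0.804 for 15% against 33% and 0.867 for 10% against 28%. Using an unpaired test therefore changes nothing in the sizing.

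**2. McNemar across arms, borderline data.**
Take 13/88 (14.8%) against 25/88 (28.4%), an illustrative difference of 13.6 points.

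- Pearson chi-square, 1 df, no continuity correction: 4.83, p=0.028.
- Exact McNemar: if k pairs have both members regular, the discordant counts are b=13−k and c=25−k, and p = 2 × P(Bin(b+c, ½) ≤ b). The value of k depends only on who is paired with whom.

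| k | b, c | exact p |
|---|---|---|
| 0 | 13, 25 | 0.073 |
| 2 | 11, 23 | 0.058 |
| 3 | 10, 22 | 0.0501 |
| 4 | 9, 21 | 0.043 |
| 6 | 7, 19 | 0.029 |
| 10 | 3, 15 | 0.0075 |

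Over randomly sampled pairings, p ran from 0.0075 to 0.073 (5th to 95th percentile 0.029 to 0.065), and about 54% of pairings fell below 0.05. The data are identical throughout.

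**3. McNemar across arms at the planned difference.**
The largest exact p over all possible pairings occurs at k=0:

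- 9/88 against 25/88 (about 10% against 28%): b=9, c=25, p=0.009.
- 13/88 against 29/88 (about 15% against 33%): b=13, c=29, p=0.020.

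No pairing loses significance at 0.05 here. The dependence on pairing matters for moderate differences, not at the design effect.

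**4. McNemar within participants.**
Assume no difference between arms, a fall from 15% regular at week 8 to 10% at week 16, and 5% to 8% regular at both. The discordant proportions are then 10% and 5%, or 7% and 2%. In 20,000 simulated trials the test (chi-square form) rejected in 21% to 32% of cases for one arm of 88, and in 79% to 95% with all 440 (5 × 88) pooled. These rejections reflect decline over time; there is no group effect to detect.

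**The case against.** A reader might infer that McNemar is the primary test of the binary outcome, or its only unadjusted test, and that the error therefore undermines the main analysis or the sample size. The document does not support that. No section calls McNemar primary. The only models labelled main are equations 1 and 2; equation 1 is itself unadjusted, covers the same outcomes, and belongs to a class of method suited to independent arms. The sizing is already an independent-groups calculation.

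Three further points count against a severe reading:

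- The article nowhere proposes pairing participants between arms, so the across-arm calculation is hypothetical, and the example chosen is close to the boundary.
- Arbitrary random pairing does not inflate type I error. In simulation with 15% in both arms of 88, the chi-square form of McNemar rejected in 5.4% and the exact form in 3.0%. The objection to it is that the answer is arbitrary.
- The likeliest explanation is loose wording that merged within-person change with group comparison. The article refers to Multimedia Appendix 1 for more on the analysis; it is not shown and may say so.

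All of this limits the consequence. None of it makes the sentence correct. It assigns McNemar to study-group differences, which the test cannot assess in this design, and an appendix would not change what the article states.

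**Conclusion.** The point holds, with limited reach. A test named for group differences in a primary binary outcome does not fit the unmatched parallel design. Across arms, a borderline comparison can fall on either side of 0.05 according to the pairing (about 0.008 to 0.073 for 13/88 against 25/88, where chi-square gives 0.028). Within participants, the test answers a question about time. At the planned 18-point difference the choice of pairing would not change significance.

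The main logistic analyses and the sample size stand unaffected by this error, so it is a secondary but real fault.

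The conclusion about the test rests on the design alone. The figures rest on assumptions: two-sided 0.05, 88 per arm, illustrative event counts, and, for the within-participant case, a fall from 15% to 10% with 5% to 8% regular at both weeks.

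**What to change.** Remove McNemar from the sentence on study-group differences. For the unadjusted comparison, refer to the logistic model of equation 1, with a global 4-df test of the four treatment coefficients and the contrasts that answer Hypotheses 1 and 2. A Pearson chi-square test, or Fisher's exact test where cells are sparse, would serve equally; the global chi-square over five arms tests the same hypothesis and agrees with the model-based test in large samples.

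If McNemar is wanted, state expressly that it only describes within-participant change from week 8 to week 16 and is not used to compare arms.

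The cost is one sentence. Data collection, design and sample size do not change.
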